## Methods/Design

### **Study design**

The trial is conducted as a national multicenter, randomized, double-blind, and placebo-controlled phase III trial using a confirmatory approach. By applying a parallel group design, the participants are randomly assigned in a 1:1 ratio to either the intervention group or to the control group. Recruitment is carried out in three large German rehabilitation clinics and is assumed to take approximately 24 months. The list of trial sites can be obtained from the German Clinical Trials Register (DRKS00019907).

The trial protocol and this manuscript have been developed in line with the Standard Protocol Items: Recommendations for Interventional Trials (SPIRIT) guideline [17].

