### **Outcomes and endpoints**

The trial outcomes have been chosen in order to determine the efficacy and the safety of the intervention.

The primary outcome **fatigue** will be evaluated by using the **Functional Assessment of Chronic Illness Therapy-Fatigue (FACIT-F) fatigue subscale**, version 4.0, a commonly used and well-validated measure of fatigue in people with cancer and other chronic health conditions [18]. The tool assesses self-reported tiredness, weakness, and difficulty conducting common activities due to fatigue. Higher scores represent less fatigue. The primary endpoint will be measured as the mean difference in FACIT-F fatigue subscale between intervention and placebo group at trial week 13–16. A mean difference of ≥3 FACIT-F fatigue subscale points will be considered a clinically relevant difference [19]. Additionally, the mean difference in change of FACIT-F fatigue subscale from baseline to trial week 13–16 between intervention and placebo group will be determined as a secondary endpoint.

**Subdomains of fatigue** will be evaluated using the **European Organization for Research and Treatment of Cancer – Cancer related Fatigue (EORTC QLQ-FA12) questionnaire.** This is an alternative to the FACIT-F fatigue subscale without being a global fatigue assessment tool [20, 21], with higher scores representing more severe fatigue. Items which are relevant for the VICTORIA study include physical, emotional and cognitive fatigue domains. They will be assessed as the mean differences in EORTC QLQ-FA12 physical, emotional and cognitive fatigue scores between intervention and placebo group at trial week 13–16 as well as mean differences in changes in these scores from baseline to trial week 13–16 between intervention and placebo group.

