#### *Randomization and blinding*

The pharmacy of the Heidelberg University Hospital manages randomization by assigning each medication package a unique three-digit number according to a randomization list. The list is created using the randomization software “RITA – Randomization in Treatment Arms” (Version 1.31) before the actual manufacturing of the study medication and is kept sealed at the coordinating center until completion of the trial. Thus, trial physicians, medical staff, patients, and staff of the coordinating center including biometricians and scientists are blinded throughout the trial. The drug packages will be sent to the trial sites in blocks of six with equal numbers of verum and placebo packages to ensure block randomization. Stratification by study center will be ensured. Trial physicians will assign the intervention blindly by taking the medication package next in row from the open block. In addition to the trial medication, the study sites will receive a sealed envelope for each randomization number with information on whether the corresponding drug package comprised verum or placebo. The envelopes will be kept at the respective study centers and remain closed, except in case of emergency unblinding due to safety reasons (e.g. safety parameters meet stopping criteria). While the trial is ongoing, the clinical monitor will check the presence and intactness of the envelopes regularly. After completion of the clinical trial, intentional unblinding is performed by combining the documentation at the trial sites with the information of the pharmacy’s randomization list.

For safety reasons, multiple laboratory tests have to be conducted in the course of the trial. In order to avoid accidental unblinding of the study staff at the trial sites and the coordinating center by knowledge of a patient’s serum 25(OH)D, serum calcium or urinary calcium levels, pseudonymized laboratory test results will be sent to a medical documentarist at the coordinating center who has no access to patient-identifying data or further pseudonymized research data collected within the trial. The medical documentarist will check the safety parameters and will inform the study sites if any of the stopping criteria are met.

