### **Statistical analysis plan**

#### Sample size estimation

The sample size calculation is based on the primary endpoint FACIT-F fatigue subscale. We assume that the FACIT-F fatigue subscale is approximately normally distributed. An increase in the FACIT-F fatigue subscale by three points was found to be a clinically relevant reduction of fatigue [19]. The assumed mean and standard deviation of the FACIT-F fatigue subscale are taken from the representative study of Jones et al. [4], which were 38.5 and 10.8, respectively. With a significance level of 0.05 and 80% power, 205 patients are needed in each group to detect a score difference of three or more points using a two-sample t-test for the mean difference, i.e. 410 patients are required in total. The number of patients to be randomized was calculated assuming a 10% drop-out rate. With these assumptions 500 CRC patients need to be screened and 456 eligible persons randomized to achieve the analyzable sample size of *n* = 410.

Given the annual number of overall 1400 eligible CRC patients reported by the participating three rehabilitation clinics in 2016, recruiting of 456 eligible stage I-III CRC patients should be feasible within 24 months.

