### Statistical methods

All analyses will be done using SAS software version 9.4 or higher. Homogeneity of the treatment groups will be described by comparison of the demographic data and the baseline values of key variables. All statistical tests will have a two-sided significance level of 0.05. Besides, 95% confidence intervals will be estimated for all outcomes in the placebo and verum group.

The primary analysis will test the null hypothesis.

H_0_: The FACIT-F fatigue subscale at week 13–16 is the same in the two groups.

versus the alternative hypothesis.

H_1_: The FACIT-F fatigue subscale at week 13–16 is different in the two groups.

The primary endpoint FACIT-F fatigue subscale will be analyzed with an intention-to-treat approach. The intention-to-treat population will include all randomized study participants with data for the primary endpoint and who did not withdraw consent during the trial. A per-protocol analysis will be done additionally as a sensitivity analysis. The per-protocol population will exclude study participants who meet the following criteria:
Fatigue questionnaire missing at trial week 13–16Error in timing of collection of fatigue questionnaire at trial week 13–16After enrollment, it becomes evident that patient met exclusion criteria at time of recruitment or did not meet inclusion criteria.Incompliance to trial medication (defined as intake of less than 80% of capsules) unless treatment was terminated due to safety reasonsSelf-reported intake of vitamin D or vitamin D analogs in addition to the trial medication.Criteria for discontinuation of study medication were met but study medication intake was continued.

We will test on normal distribution for the outcome FACIT-F fatigue subscale with the Shapiro-Wilks test. If normal distribution can be assumed, the primary test statistic will be the two-sample t-test for the mean difference. If normal distribution cannot be assumed for the FACIT-F fatigue subscale, we will log-transform the FACIT-F fatigue subscale and test for normal distribution once more with the Shapiro-Wilks test. If normal distribution can neither be assumed for FACIT-F fatigue subscale nor log-transformed FACIT-F fatigue subscale, a Wilcoxon Rank-Sum test will be applied. In addition, appropriate 95% confidence intervals will be estimated for the FACIT-F fatigue subscale in the two groups and for the difference in FACIT-F fatigue subscale between the two groups.

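### The primary test leaves out the screening FACIT-F score and the stratifying centre; a baseline- and centre-adjusted ANCOVA would gain precision without adding patients

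*Protocol article*

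**What the plan says.** All references are to the protocol article.

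- **Primary test (Statistical methods).** The null hypothesis is that the week 13–16 FACIT-F fatigue score is the same in both groups. A Shapiro-Wilk test chooses the method: "If normal distribution can be assumed, the primary test statistic will be the two-sample t-test for the mean difference". Otherwise the score is log-transformed and tested for normality again, and if that fails too, a Wilcoxon rank-sum test is used. No branch names a covariate.
- **Sample size (Sample size estimation).** The number per arm is worked out for that same unadjusted t-test and a 3-point target: "With a significance level of 0.05 and 80% power, 205 patients are needed in each group". The assumed mean and SD are those of a single score, "which were 38.5 and 10.8, respectively".
- **Screening score.** Table 3 schedules fatigue at screening and again in weeks 13–16. The screening score is used as a subgroup factor, as a covariate in a sensitivity regression, and in a secondary endpoint, the "mean difference in change of FACIT-F fatigue subscale from baseline to trial week 13–16 between intervention and placebo group" (Outcomes and endpoints).
- **Centre (Randomization and blinding).** Packages go to the three clinics in blocks of six: "Stratification by study center will be ensured". Centre appears in none of the fatigue analyses. It is a covariate only in the exploratory model for achieved 25(OH)D.
- **Sensitivity regression (Statistical methods).** It adjusts for every variable in the subgroup list. That list includes therapy during the trial and, all at follow-up, depression score, insomnia, pain, and use of strong opioids, psycholeptics and systemic corticosteroids.

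**The concern.** A patient's fatigue at screening will usually predict fatigue three to four months later. An unadjusted comparison leaves that predictable variation in the error term. Three things follow.

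1. The confidence interval is wider than it needs to be, and power is lower than the same patients could give.
2. A chance difference between the arms in screening fatigue passes into the primary estimate in proportion to the correlation, with nothing in the primary model to remove it.
3. A factor that constrains the randomization is absent from the analysis. This tends to make the test slightly conservative.

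The planned regression does not fill the gap. Several of its covariates are measured after treatment has started and could be affected by it; depression is itself a secondary efficacy outcome. Conditioning on them can remove part of a real effect or distort it, so the coefficient is not a plain baseline-adjusted treatment effect. The change-score endpoint does use the screening score, but it fixes the baseline slope at 1 instead of estimating it.

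**Working it through.** **Inputs from the protocol article:** difference 3 points and SD 10.8 (Sample size estimation); two-sided 0.05, since "All statistical tests will have a two-sided significance level of 0.05" (Statistical methods); patients "randomly assigned in a 1:1 ratio" (Study design); 205 analysed per arm.

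**Assumed input:** the correlation r between screening and week 13–16 scores. The document does not give it. One range, 0.3 to 0.7, is used for every comparison below, with the same SD at both times.

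**Step 1: reproduce the plan's figure.** The normal approximation gives 2 × (1.960 + 0.842)² × 10.8² / 3² = 203.4, so 204 per arm. With the noncentral t distribution, power is 79.9% at 204 and 80.1% at 205. The stated 205 is right. Allowing for 10% drop-out, 410 / 0.9 = 455.6, so 456 randomized, also as stated.

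**Step 2: unadjusted precision.** Standard error = 10.8 × √(2/205) = 1.067. The 95% half-width is 1.96 × 1.067 = 2.09 points.

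**Step 3: the alternatives at 205 per arm.**

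- ANCOVA: residual SD = 10.8 × √(1 − r²). Power uses the noncentral t with three fewer degrees of freedom (screening score and two centre terms).
- Change score: SD = 10.8 × √(2(1 − r)).
- Half-width = 1.96 × residual SD × √(2/205).

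| r (assumed) | ANCOVA residual SD | ANCOVA half-width | ANCOVA power | Change-score power | Unadjusted power |
|---|---|---|---|---|---|
| 0.3 | 10.30 | 1.99 | 83.7% | 66.0% | 80.1% |
| 0.4 | 9.90 | 1.92 | 86.5% | 72.6% | 80.1% |
| 0.5 | 9.35 | 1.81 | 90.0% | 80.1% | 80.1% |
| 0.6 | 8.64 | 1.67 | 93.9% | 88.0% | 80.1% |
| 0.7 | 7.71 | 1.49 | 97.6% | 95.2% | 80.1% |

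The change score is worse than the unadjusted test below r = 0.5 and better above it. ANCOVA beats both throughout this range. Read the other way, at r = 0.5 ANCOVA would reach 80% power with about 153 per arm (normal approximation).

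**Step 4: centre alone.** If centre explained 1%, 2% or 5% of the variance (assumed), adding it alone would give power of 80.5%, 80.9% or 82.1%.

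**Step 5: chance imbalance.** Taking SD 10.8 at screening too, the difference in screening means has standard error 1.067, so imbalances up to about 2.1 points lie within its 95% range. At r = 0.5, a 2-point imbalance shifts the expected unadjusted estimate by 0.5 × 2 = 1 point, one third of the 3-point threshold for clinical relevance. ANCOVA takes this out.

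**The case against.** The strongest reply is that nothing here is wrong. Randomization makes the unadjusted t-test valid, the sample size was computed for exactly that test, and the two agree. That stands in full. A reader might infer that the trial is underpowered, biased or at risk of an inflated type I error; the document supports none of these.

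Other limits also stand:

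- **The size of the gain is conditional.** A figure such as 87% to 94% holds only for r of about 0.4 to 0.6. With no correlation in the document, it cannot be stated as a fact. At r = 0.3 the gain is under 4 percentage points.
- **The change score is not always poor.** For r of 0.6 to 0.7 it has 88% to 95% power, above the unadjusted test.
- **Centre is not a source of power.** Step 4 shows how little it adds.
- **Secondary endpoints.** A reader might infer that they get no adjusted analysis at all. Right after describing the regression, Statistical methods applies the primary endpoint's methods to the continuous secondary endpoints. That can be read as including the regression, so the inference is not secure.
- **Competing primary answers.** A reader might see two rival results for fatigue. Outcomes and endpoints makes the week 13–16 difference primary and the change expressly secondary, so there is one confirmatory result.
- **Imbalance is partly covered** by the baseline comparison, the change endpoint and the regression, though none of these is the primary estimate.

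What the reply does not answer is why a covariate already collected for every purpose except the primary test should be left out of it.

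**Conclusion.** The point holds as a free improvement. The primary analysis is valid and correctly sized, but it does not use the screening FACIT-F score or the stratifying centre, and no other planned analysis gives a clean baseline-adjusted estimate of the treatment effect on fatigue.

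For r between 0.3 and 0.7, adjusting would raise power at 205 per arm from 80% to about 84% to 98% and shorten the 95% half-width from about 2.1 points to between 2.0 and 1.5. These figures rest on the assumed correlation, the protocol's SD of 10.8 at both times and its 3-point difference. They are set against the t-test branch only; the log-transform and Wilcoxon branches were not evaluated. The direction of the gain does not depend on the exact r within this range; its size does.

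**What to change.** **Primary analysis.** Use an ANCOVA of week 13–16 FACIT-F on treatment, screening FACIT-F (continuous) and study centre. Report the adjusted mean difference with its 95% confidence interval and read it against 3 points. State that this replaces the whole Shapiro-Wilk, log-transform and Wilcoxon sequence, not only its t-test branch, so that the estimate stays in FACIT-F points whatever the distribution looks like.

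**Sensitivity analyses.** Keep the unadjusted t-test and the Wilcoxon test.

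**Secondary endpoints.** Use the same model for continuous endpoints that have a baseline value. Once baseline is a covariate, modelling the follow-up value or the change gives the same treatment coefficient, so one result can stand in place of the two separate tests.

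**Cost.** No extra patients, visits or data, and the sample size is unchanged. Because the test is fixed in the protocol text, this is more than a wording change in an analysis plan. It may be a substantial change, which under Quality control and assurance needs four signatures (sponsor, coordinating investigator, biometrician, clinical pharmacology consultant) and submission to the Ethics Committee and the competent authority. Trial status puts the start of recruitment after submission of the article, and no interim analysis of the primary outcome is planned, so the change can be prespecified before any outcome data exist.

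### A Shapiro-Wilk pre-test chooses the primary test, and two of its three branches do not test the mean difference that defines the endpoint and sizes the trial

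*Protocol article*

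**What the plan says.** Under Outcomes and endpoints, the protocol article defines the primary endpoint as a difference in means: "The primary endpoint will be measured as the mean difference in FACIT-F fatigue subscale between intervention and placebo group" at week 13-16. The benchmark is on the same scale: "A mean difference of ≥3 FACIT-F fatigue subscale points will be considered a clinically relevant difference".

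Under Sample size estimation, the trial is sized for that quantity: "With a significance level of 0.05 and 80% power, 205 patients are needed in each group to detect a score difference of three or more" (scale units, by a two-sample t-test). The score is assumed approximately normal, and the mean and SD come from a cited study, "which were 38.5 and 10.8, respectively".

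Under Statistical methods, the test is not fixed. The outcome first goes through Shapiro-Wilk: "If normal distribution can be assumed, the primary test statistic will be the two-sample t-test for the mean difference". If it fails, the score is log-transformed and tested for normality again. The last step is: "If normal distribution can neither be assumed for FACIT-F fatigue subscale nor log-transformed FACIT-F fatigue subscale, a Wilcoxon Rank-Sum test will be applied". The null hypothesis there speaks of equality of the subscale between groups and does not name the mean. A 95% confidence interval for the between-group difference is promised in every branch. The same methods apply to all continuous secondary endpoints.

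**The concern.** The trial is described as confirmatory, but three different tests could become its primary test, and the outcome data decide which one. Only the t-test on untransformed scores addresses the stated endpoint. A t-test on log scores compares geometric means, so its result is a ratio and cannot be read against 3 points. The Wilcoxon test responds to the tendency of one arm to score higher than the other, which can move differently from the mean when scores are skewed.

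At stake is the meaning of the primary p-value. It could be significant while the interval for the mean difference includes zero, or the reverse, and the plan would have no single answer. The 80% power also describes only one of the three branches.

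**Working it through.** **Inputs from the article.** Two-sided alpha 0.05, 80% power, difference 3, mean 38.5, SD 10.8, 1:1 allocation, 10% drop-out.

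**Reproducing the plan's figure.** Normal approximation: n = 2 × 10.8² × (1.960 + 0.842)² / 3² = 203.4, so 204 per arm. The t-based solution is 204.4, so 205 per arm, with power 80.1%. Total 2 × 205 = 410, and 410 / 0.90 = 455.6, so 456 randomised. The stated figures are right, for the t-test.

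**Simulating the sequence.** There were 205 patients per arm and 3,000 runs per scenario (Monte Carlo standard error about 0.7 points on power and 0.4 on type I error).

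Assumptions not in the article:
- Shapiro-Wilk is run at 0.05 on the pooled 410 scores. Testing each arm, or the residuals, gave the same pattern.
- The log is log(x + 1).
- The scale's upper limit is not given, so it is varied. A limit of 52 would lie (52 − 38.5) / 10.8 = 1.25 SD above the mean.

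| Score distribution (SD 10.8) | Shapiro-Wilk rejects raw scores | Type I error, whole sequence | t power | Wilcoxon power |
|---|---|---|---|---|
| Normal (the plan's assumption) | 5% | 4.7% | 81.5% | 79.2% |
| Normal, rounded to integers | 8% | 5.2% | 79.9% | 76.9% |
| Beta, upper limit 52 | 100% | 5.7% | 79.8% | 95.5% |
| Beta, upper limit 60 | 100% | 5.4% | 79.5% | 81.5% |
| Beta, upper limit 80 | 28-29% | 5.0% | 80.6% | 78.4% |
| Beta, upper limit 100 | 40-51% | 4.9% | 80.4% | 78.8% |
| Normal, clipped at 52 | 100% | 4.5% | 78.1% | 77.4% |

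Power is for means of 38.5 and 41.5. In the clipped row the shift of 3 is before clipping, and the observed mean difference is 2.6.

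**What the table shows.**
- Log scores failed Shapiro-Wilk in 99.9-100% of runs in every scenario. The log step is practically dead, and the real alternative to the t-test is Wilcoxon.
- The t-test's own type I error was 4.8-5.8% in all null scenarios. These include a truncated normal with skewness −1.0 (5.8%) and the beta with limit 52, skewness about −0.86 (5.3%). It does not need the gate.
- With the beta and limit 52, a mean difference of 3.0 goes with a median difference of 4.2, so different summaries of the same data give different sizes of effect.

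**When the benefit is not uniform.** The subgroup section counts a screening score of 34 or less among the conditions for profiting most. Benefit was therefore confined to such patients, with limit 52, a mean difference of 3 and an assumed screening-to-follow-up correlation:
- Correlation 0.5, 0.6, 0.7: t 85%, 87%, 88%; Wilcoxon 85%, 83%, 78%. The t-test alone was significant in 3%, 5% and 11% of trials.
- A second set of runs over 0.5-0.7 gave t 86-89%, Wilcoxon 79-87%, and t alone significant in 2-10%.
- A third, built differently, gave t 78-87%, Wilcoxon 77-79%, and conflicting conclusions in 5-11%.

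So Wilcoxon gains under a uniform benefit near a limit of 52 (about 90-95% against about 80%), and tends to lose when the benefit sits in the more fatigued patients.

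**The case against.** The best defence is that the sequence is ordered, complete and pre-specified. Nobody chooses the test after seeing results, and the simulated type I error of the whole sequence is 4.5-5.7%. Wilcoxon is also a valid test of the null hypothesis as literally worded. The article promises a 95% confidence interval for the difference in every branch and adds a linear regression on the subscale, so an effect in points can still be set against 3. All of this stands. It limits the harm but does not align the primary test with the endpoint, because the interval and the regression are supportive results.

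Three stronger readings are tempting, and the documents support none of them.

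- *The t-test will almost certainly be dropped.* This needs the scale's upper limit, which the article does not state. Under its own normality assumption the t-test survives in 92-95% of trials.
- *The switch costs much power.* Wilcoxon power near 54-55% against 91-92% for t, with t alone significant in 35-37% of trials, does appear in simulation, but only if benefit depends on each patient's own untreated week 13-16 score. That amounts to a correlation of 1 with screening and gains of about 10 points in 30% of patients. The article defines the group by the screening score.
- *The pre-test inflates the false-positive rate.* The simulations show no inflation.

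**Conclusion.** The point holds as a mismatch between test and endpoint, and should be fixed. Three places disagree: the endpoint and the sample size concern a mean difference tested by t-test, while the analysis section may replace that test with one of a different quantity, at unstated power. This follows from the article alone.

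The size of the problem depends on assumptions. The t-test is dropped in about 5-8% of trials under approximate normality, in 28-51% with an assumed upper limit of 80-100, and in about 100% with 52-60. At a true mean difference of 3 and an assumed limit of 52, Wilcoxon has about 90-95% power against about 80% for t if the benefit is uniform. If the benefit is confined to patients at or below 34 at screening (assumed correlation 0.5-0.7), most runs give Wilcoxon about 78-87% against about 85-89% for t. No loss of power or error control is therefore demonstrated. What is lost is a single, fixed primary question.

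**What to change.** In Statistical methods, for the primary endpoint:

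1. Delete the Shapiro-Wilk and log-transformation steps.
2. Make the comparison of mean untransformed FACIT-F fatigue scores at week 13-16 the single primary analysis whatever the distribution, by two-sample t-test (the Welch form is acceptable), with a 95% confidence interval for the mean difference.
3. State the null and alternative hypotheses in terms of group means.
4. Report the Wilcoxon test as a sensitivity analysis only.

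The continuous secondary endpoints inherit the same sequence, so say explicitly whether the change extends to them.

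The cost is wording, to be settled before unblinding. The sample size stays at 456 and no extra data are needed. There is one small downside: if the benefit is a uniform shift and scores crowd near an upper limit, Wilcoxon would have had more power than the t-test's 80%.

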As a sensitivity analysis, a linear regression model will be carried out with FACIT-F fatigue subscale as the dependent variable and treatment group as the independent variable. The linear regression model will be adjusted for all variables named in the subgroup analysis while using some variables continuously instead of categorically (age, hemoglobin levels at screening, 25(OH)D levels at screening, BMI at screening, FACIT-F fatigue subscale at screening, insomnia scale at follow-up and pain scale at follow-up). If appropriate, missing covariate values will be imputed with multiple imputation.

All secondary endpoints with a continuous scale will be analyzed with the same statistical methods as described for the primary endpoint. All dichotomous secondary endpoints will be tested with a Chi^2^ test. AEs will be analyzed with descriptive statistics including frequencies of SAEs.

Lastly, the success of the personalized vitamin D_3_ intervention in raising the serum 25(OH)D level will be evaluated in the intervention group at trial day 12–21. Furthermore, the success of the maintenance dose to maintain sufficient vitamin D status in the intervention group will be evaluated in trial week 13–16. To be successful, the mean 25(OH)D levels in the group with personalized vitamin D_3_ intervention should be higher than 50 nmol/L. This translates into the following test hypotheses:
H_0_: Mean 25(OH)D_personalized intervention_ ≤ 50 nmol/LH_1_: Mean 25(OH)D_personalized intervention_ > 50 nmol/L

To test these hypotheses, we will conduct a one-sample t-test on the mean 25(OH)D levels at a one-sided significance level of 0.025. 25(OH)D levels may be log-transformed if this improves the approximation of a normal distribution (to be tested with a Shapiro-Wilks test).

*Exploratory sub-project: “Determinants of the achieved 25(OH)D levels by the personalized vitamin D*_*3*_*intervention”*

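### A normality check on the outcome chooses the primary test, and two of its three branches do not test the mean difference on which the endpoint and sample size rest

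*Protocol article*

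**What the plan says.** Under Outcomes and endpoints, the endpoint is a contrast of means: "The primary endpoint will be measured as the mean difference in FACIT-F fatigue subscale between intervention and placebo group at trial week 13–16". A difference of 3 points or more is called clinically relevant.

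Under Sample size estimation, the calculation assumes approximate normality with a mean and SD "which were 38.5 and 10.8, respectively". It states "With a significance level of 0.05 and 80% power, 205 patients are needed in each group" and names the planning test: "to detect a score difference of three or more points using a two-sample t-test for the mean difference".

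Under Statistical methods, the primary test is chosen in steps. Shapiro-Wilk is applied to the outcome, and if normality is accepted a two-sample t-test is used. Otherwise: "If normal distribution cannot be assumed for the FACIT-F fatigue subscale, we will log-transform the FACIT-F fatigue subscale", followed by a second Shapiro-Wilk test. If both checks fail, the test is a Wilcoxon rank-sum test. No test is named for the case in which the logged score passes; a t-test on logs is presumably meant. The text does not say whether normality is checked on the pooled sample or in each arm.

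The same section carries the rule over to other outcomes: "All secondary endpoints with a continuous scale will be analyzed with the same statistical methods as described for the primary endpoint". These include changes from baseline and possibly infection counts, if those are treated as continuous.

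**The concern.** The trial is described as confirmatory, so its test should follow from its endpoint. Here the endpoint, the 3-point criterion and the sample size all concern a difference in means, while the test depends on the shape of the observed data. A t-test on logs compares geometric means, and a Wilcoxon test compares ranks. Either can give a p-value that disagrees with the confidence interval for the mean difference, and the protocol does not say which would then govern.

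A fatigue score with a ceiling not far above its mean is likely to be left-skewed. Such a score fails the first check in a sample of 410, and taking logs stretches the lower tail and makes left skew worse. In that case the test that was powered would rarely be the test that is run.

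**Working it through.** **1. The protocol's own figure.** Inputs from Sample size estimation: difference 3, SD 10.8, power 80%, drop-out 10%. From Statistical methods: "All statistical tests will have a two-sided significance level of 0.05".

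n per group = 2(1.960 + 0.842)² × 10.8² / 3² = 2 × 7.85 × 12.96 ≈ 203.4, so 204 by the normal approximation. With the exact noncentral t, power is 79.9% at 204 and 80.1% at 205. Hence 205 per group and 410 in total; 410 / 0.90 = 455.6, so 456 randomized. The stated 205 / 410 / 456 is reproduced, for the t-test.

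**2. What each branch tests.**
- Raw t-test: difference in means, as in the endpoint definition.
- Analysis of logs: ratio of geometric means.
- Wilcoxon: whether scores in one arm tend to be higher than in the other.

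Only the first matches the endpoint.

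**3. How often each branch is reached.** The protocol gives neither the maximum nor the skewness of the score, so the maximum is an assumption and is varied. At an assumed maximum of 52, the ceiling is (52 − 38.5) / 10.8 = 1.25 SD above the mean; a normal distribution would put 10.6% of patients above it. Simulation: 205 per arm, means 38.5 and 41.5, SD 10.8, Shapiro-Wilk at 0.05 on the pooled sample, log(score + 1), 2,000 runs (Monte Carlo error about 0.9 points on power).

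| Assumed distribution | t / log / Wilcoxon chosen (%) | t-test power | Wilcoxon power |
|---|---|---|---|
| Integer beta, max 52 | 0 / 0 / 100 | 79.9% | 94.2% |
| Normal clipped at 52 | 0 / 0 / 100 | 78.6% | 78.6% |
| Integer beta, max 60 | 0 / 0 / 100 | 80.2% | 81.5% |
| Integer beta, max 80 | 74 / 0 / 26 | 79.6% | 77.5% |
| Integer beta, max 100 | 60 / 0.3 / 39 | 78.7% | 76.9% |
| Exactly normal | 94 / 0 / 6 | 79.6% | 78.4% |
| Normal, rounded | 92 / 0 / 8 | 78.9% | 76.5% |

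With no true difference, Wilcoxon was chosen in 29% of runs at maximum 80 and 53% at maximum 100. Checking each arm separately gave the same pattern; under normality it raised the Wilcoxon share to 9–13%. The type I error of the whole procedure was 4.4–5.6%.

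**4. The log step.** In the maximum-52 case skewness is about −0.85 on the raw score and about −2.0 after the log. A t-test on logs would have had 59.5% power there, but the branch was not reached.

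**5. Where the benefit falls.** Same maximum-52 distribution, 205 per arm; the rule chose Wilcoxon in every run.
- Verum mean 3 points higher at the same SD: t-test about 79–82%, Wilcoxon about 94–96%.
- The same mean benefit confined to patients who would score 34 or less: about 31% of patients fall there, so each gains 3 / 0.313 ≈ 9.6 points. T-test 91%, Wilcoxon 54%. Rounding the gain to 10 points gives 94% and 60%.

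The second case takes the untreated follow-up score as a stand-in for the screening score. It is relevant because Statistical methods lists a screening score of 34 or less among the conditions marking the patients most likely to profit.

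**6. Is the gate needed?** No. In the bounded, left-skewed case the ungated t-test kept 5.0% type I error and 79.9% power.

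**7. Change scores and counts.** The log does not exist for changes of zero or below, or for zero counts, so that step cannot be carried out as written. The rule was simulated at n = 410 with logs of positive values only, for normal, heavy-tailed and bounded change scores and for Poisson and negative binomial counts. The log branch was chosen in 0% of runs. Normal changes went to the t-test in 88–92% of runs and otherwise to Wilcoxon; counts always went to Wilcoxon.

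**The case against.** The cascade is written down in advance and fully ordered, so it leaves the analyst little discretion, and it does not inflate type I error. The null hypothesis as worded says only that the subscale is the same in both groups, which a rank test can address. A 95% confidence interval for the between-group difference is promised whichever test is used, and a linear regression on the raw score is planned as a sensitivity analysis. The 3-point criterion can therefore still be examined. All of this stands, and it limits the harm. It does not remove the mismatch, because the endpoint definition names the mean and the confirmatory p-value may come from a test of something else.

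Three stronger readings are tempting but not supported:
- **A Wilcoxon test is practically certain.** That needs a ceiling close above the mean. The protocol states no range and assumes approximate normality, under which the t-test is kept in about 92–94% of runs with a pooled check.
- **Power is lost.** Wilcoxon power was 77–94% in the settings of the table, and in the bounded cases (maximum 52 or 60) equal to or above the t-test. It falls well below only when the benefit is concentrated in low scorers, which is one chosen scenario.
- **Patients without improvement or without infections are dropped because their logs are undefined.** Logged values are analysed only if they pass the second check. In simulation they never did, and the t-test or Wilcoxon test then uses everyone.

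**Conclusion.** The point holds as a mismatch between endpoint and test. The protocol fixes a mean-difference endpoint and a t-test sample size, then lets the outcome data choose among three tests, two of which do not test that mean difference.

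The stated 80% power describes the t-test alone. If Wilcoxon is selected, power depends on where the benefit falls: about 95% or about 54–60% for the same 3-point mean benefit, at an assumed maximum of 52. The frequency of selection rests on the unstated range of the score and, for maxima of 80 or 100, on whether a true difference exists. Type I error is not at issue. For change scores and counts the log step is a defect of wording, with no demonstrated effect on who is analysed.

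**What to change.** Delete the Shapiro-Wilk, log and Wilcoxon cascade. Name the difference in means at week 13–16 as the single primary test whatever the distribution, using either the two-sample t-test on which the trial was sized or an ANCOVA on the baseline score. Keep Wilcoxon as a sensitivity analysis. State the null hypothesis in terms of means, and state that the confidence interval for the mean difference comes from the same analysis as the p-value. For secondary endpoints, do not log-transform change scores or counts.

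The cost is a change of wording, made before the treatment groups are compared. The 205 / 410 / 456 figures are unchanged. The small downside is that Wilcoxon would have been the more powerful test under some shapes of benefit.
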